### **3.4 Methods against bias**

For logistical reasons, clusters of 4-6 eligible patients at a time will be randomised to group psychotherapy according to the IPT-Work or SP condition. To avoid selection bias, the raters who identify eligible patients and obtain informed consent will not be informed about the randomisation result, nor about ongoing or previous IPT-Work or SP psychotherapy groups at their respective centre.

To further avoid selection bias, the randomisation code to allocate patient groups to interventions will be generated by the CTU using the following procedure to ensure that treatment assignment is unbiased and concealed from patients and site staff. Randomisation of patient groups will be performed, stratified by centre, in blocks of variable length with a 1:1 ratio. The block lengths will be documented separately and will not be disclosed to the centres. The randomisation code will be produced by validated programmes based on the Statistical Analysis System (SAS).

Obviously, blinding of patients and study psychotherapists performing the interventions is not possible. However, data acquisition other than patient reported outcomes will be done by trained blinded clinical raters not involved in patient management. Each site will implement procedures to mask patient treatment assignment from the clinical rater by reminding the patients at each visit not to mention anything that might reveal their treatment condition. Diagnostic training of raters in the SCID-5, HRSD-24 and (S)AE assessments will be conducted by expert trainers and interrater reliability will be ensured. The other measures are self-rated in a standardised questionnaire format.

All confirmatory analyses are fully specified in the trial protocol to avoid reporting bias. The trial is registered prospectively at the German Clinical Trials Register (see chapter 13), and its results will be published irrespective of the outcome to prevent publication bias.

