| Therapeutic element checklist (Stundenbogen)**                                 |                      |                    | x           | x           | x           | x           | x           | x           |                |                         |
| Change of medication/therapy**                                                 |                      |                    |             |             |             |             |             |             | x              | x                       |
| Adverse Events / Serious Adverse Events**                                      |                      |                    | x           | x           | x           | x           | x           | x           | x              | x                       |

\*Self-rated by patient \*\* After informed consent

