### **5.3.1 General procedures in both study arms**

Before the start of the group, in both study arms one individual preliminary talk of app. 30 minutes will be conducted in which an interpersonal inventory is performed and the indication of involvement of the employer and/or a social worker is determined (no documentation in eCRF required).

To check for adherence and to support the supervision, a ‘Therapeutic Element Checklist’ (Stundenbogen) for IPT-Work (e.g. strategies for addressing work-life-balance, demand-control-balance, effort-reward-balance, and work as a social role) and SP (e.g. reflective listening,

facilitation of affect, helping the patient to feel understood) is filled out by the therapist immediately after each group session.

No additional psychotherapeutic treatment is allowed throughout the study including the follow-up visit.

Antidepressive medication is allowed if stable for at least 4 weeks before randomisation and throughout the follow-up period. The continuous intake of benzodiazepine is prohibited; the selective use of benzodiazepine as rescue medication on-demand for a maximum of 2 weeks is permitted. Other required medication for comorbid somatic diseases will be allowed and documented.

During group sessions, study psychotherapists will encourage patients to report any adverse events either during the session or confidentially. The psychotherapist will document adverse events as described in section 7.

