### **5.3.2 IPT-Work (intervention arm)**

The IPT-Work condition follows a manual and focuses on the work context by adding specific elements to the regular IPT strategies in four modules of

1. work-life-balance: identifying work-related stress factors and allostatic overload; psychoeducation on the association of work stress, social support and depression; creating a balance between performance values and interpersonal values; teaching mindfulness skills (as a different therapeutic intervention) to reduce physical and mental tension/stress,
2. demand-control-balance: enhancing communication skills at work (e.g. negotiating modified work tasks or working hours) to cope with difficult work situations; set limits to exaggerated demands (prevent allostatic overload; get a sense of control over the work conditions e.g. organisational injustice); ask for support; cope with interpersonal conflicts and difficult role transitions at the workplace,
3. effort-reward-balance: identify values at work; set self-exertion and reward in balance,
4. work as a “social role”: define your work place with strengths and limitations. The intervention includes 10 group sessions (twice weekly in the first 2 weeks, 1 weekly thereafter) of 90 minutes for 4-6 outpatients over 8 weeks.

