### **5.4.2 Post-treatment, Follow-up / End of Trial**

After end of treatment, patients will participate in two subsequent evaluations at post-treatment ( $W9 \pm 7$  days) and follow-up ( $W21 \pm 7$  days) to assess their condition after study psychotherapy. All evaluations will be conducted by the respective trained and blinded raters (preferably the same person who was responsible for the study inclusion) according to the details described above.

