## 7.2 Documentation of AEs and serious AEs (SAEs)

(Serious) adverse events have to be documented in the eCRF beginning from the date of randomisation and ending with the date of the study end.

The documentation obligation of AEs applies to the study psychotherapist or rater who first became aware of the event.

- Characterisation of the event (see above listed events, in case of “Other AEs”, a diagnosis/symptoms have to be provided, symptoms only if diagnosis not yet available)
- Onset/end date
- Severity (mild to severe)
- Relationship to study procedure
- Serious / non-serious (yes/no; yes, if one of the SAE criteria is met)
- Outcome

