### 10.5.9 Analysis of safety

Adverse events are described by main categories A-H (see section 7.1). The incidences of adverse events will be summarised in the SAF by treatment arm with two-sided 95% confidence intervals based on Wilson scores (without continuity correction) according to method 3 in Newcombe (1998).

The AEs will be displayed in summary tables by treatment as follows:

The total number of AEs, the minimum, maximum and mean number of AEs per patient will be calculated per main category A-H and in total.

The incidence of AEs defined by main categories A-H will be calculated as the number of patients who experienced at least one AE with the respective category A-H in percentage of the total number of patients.

Each table will be produced for the following AE-sets:

- All AEs
- All Serious Adverse Events (SAEs)

Additionally, these tables will be recalculated for AEs with onset during the treatment period and for AEs with onset after the treatment period.

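### The after-treatment AE tables count unobserved patients as event-free and cannot be read against the during-treatment tables, and section 3.4 misstates who collects AEs

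*Protocol*

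**What the plan says.** Section 10.5.9 summarises AEs in the safety set by treatment arm. For each category and overall it gives the total number of AEs and the minimum, maximum and mean per patient. Incidence is the "number of patients who experienced at least one AE with the respective category A-H in percentage of the total number of patients", with Wilson intervals. It then adds that "these tables will be recalculated for AEs with onset during the treatment period and for AEs with onset after the treatment period". No statistic uses observation time, and no denominator is restricted to patients still followed.

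Section 2.3 defines the safety set as all randomised patients who started group sessions. Table 3 in section 2.4 names the risk difference between arms as the AE summary and lists non-start as the only intercurrent event.

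In Table 5 (section 5), the row "Adverse Events / Serious Adverse Events" is marked at the ten sessions V2 to V11, then only at V12 (week 9) and V13 (week 21). Section 5.3.1 states: "During group sessions, study psychotherapists will encourage patients to report any adverse events either during the session or confidentially". The same section has the psychotherapist document these events. Section 7.2 places the duty to document on whichever psychotherapist or rater first learns of the event, "beginning from the date of randomisation and ending with the date of the study end".

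Section 3.4 accepts that psychotherapists cannot be blinded, but then states that "data acquisition other than patient reported outcomes will be done by trained blinded clinical raters not involved in patient management".

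**The concern.** There are three difficulties.

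1. **Denominator.** In the after-treatment table, a patient who leaves before any post-treatment contact adds nothing to the numerator but stays in the denominator. The incidence is pulled down. If loss differs by arm, the risk difference named in Table 3 moves with it.

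2. **Comparability of the two periods.** Paired tables for during and after treatment invite the reader to compare them. They cover different lengths of time and rest on different intensities of questioning, and nothing in section 10.5.9 says so. A change between them could be read as harm tied to active treatment, or as recovery, when it may reflect only calendar time and prompting.

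3. **Blinding.** Section 3.4 attributes to the AE data a blinded collection that the design does not provide during treatment. Section 7.2 asks for severity and relationship to the study procedure for each event, and someone who knows the arm may supply these entries. A reader relying on section 3.4 would take them to be blinded.

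**Working it through.** **Contacts and time (Table 5, section 5.3.2)**

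- Sessions: 2 × 2 + 6 × 1 = 10, which reproduces the stated ten and matches V2 to V11.
- During treatment: 10 contacts / 8 weeks = 1.25 per week.
- After treatment: 2 contacts / 13 weeks = 0.154 per week.
- Ratio of contact density: 1.25 / 0.154 = 8.1.
- Ratio of period lengths: 13 / 8 = 1.63, the later period being longer.

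**Denominator**

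Let p be the true after-treatment incidence and d the proportion of the safety set with no post-treatment observation, with loss unrelated to AEs. The reported incidence is p × (1 − d).

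- Section 10.4 anticipates 10% drop-out at follow-up. With p = 30% (assumed): 0.30 × 0.90 = 27%.
- The 27% is a floor under these assumptions. Some drop-outs will be seen at week 9, and patients who never start are outside the safety set. The reported value would lie between 27% and 30%. If patients with AEs were more likely to leave, it could be lower.
- Unequal loss, 5% against 15% (assumed): 0.30 × 0.95 = 28.5% and 0.30 × 0.85 = 25.5%, a difference of 3 points where none exists.
- Sampling error of a risk difference at p = 30% with 72 per arm (section 3.3): 1.96 × √(2 × 0.30 × 0.70 / 72) = 0.150, about ±15 points.

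**Do counts have to fall after treatment?**

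Assume a constant true AE rate. Assume also that each AE is recorded at the next contact with probability 2^(−lag/h), where h is a recall half-life. The protocol gives no such figure, so h is varied. A gap of g weeks between contacts then yields h/ln 2 × (1 − 2^(−g/h)) weeks' worth of recorded AEs. Sessions are placed at weeks 0.5, 1, 1.5, 2 and 3 to 8 (spacing within the first two weeks assumed) and visits at weeks 9 and 21.

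Example with h = 8, where h/ln 2 = 11.54. After treatment, the gaps of 1 and 12 weeks give 11.54 × 0.083 + 11.54 × 0.646 = 8.42. The ten sessions give 7.70. The count ratio is 8.42 / 7.70 = 1.09. The weekly rate ratio is (8.42/13) / (7.70/8) = 0.67.

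| Half-life (weeks) | Count ratio, after/during | Weekly rate ratio, after/during |
|---|---|---|
| complete recall | 1.63 | 1.00 |
| 26 | 1.42 | 0.88 |
| 13 | 1.26 | 0.77 |
| 8 | 1.09 | 0.67 |
| 6 | 0.98 | 0.60 |
| 4 | 0.80 | 0.49 |
| 2 | 0.53 | 0.33 |

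Counts fall only if capture after treatment, relative to capture during treatment, is below 8/13 = 62%. In this model that means a half-life below about 6.3 weeks. The weekly rate falls whenever recall is incomplete. Section 10.5.9 tabulates counts and percentages, so the direction of what it will show is not fixed. A patient-weeks rate removes the effect of period length but not that of prompting.

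**Who collects AEs**

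Section 3.4 gives data other than patient-reported outcomes to blinded raters, includes (S)AE assessment in their training, and describes the remaining measures as self-rated questionnaires. On that text, AEs fall on the raters' side. Sections 5.3.1 and 7.2 have the treating psychotherapist prompt for and document them. The two cannot both describe the treatment period.

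**The case against.** **Both arms share a schedule, and the tables are by arm.** This stands. Supportive therapy has the same format, frequency and duration (section 5.3.3), and no comparison between periods is planned. A reader might infer from the eightfold difference in contacts that the arm comparison is biased. The documents do not support that, because contact density is balanced by design. Equal schedules do not, however, deal with unequal loss.

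**AEs must fall after treatment.** A reader might infer this from the sparser contacts. It does not follow. The later period is 1.63 times longer, and the sign for counts depends on a recall assumption found nowhere in the protocol.

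**AE capture is wider than scheduled contacts.** This largely stands. Documentation is continuous and dated by onset, so week 9 can still pick up treatment-period events. Under section 7.4, raters also check for suicidality by interview and by HRSD-24 and BDI-II item thresholds. This reduces the gap in ascertainment by an unknown amount.

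**Therapist bias is speculative.** This stands as to size. All therapists deliver both arms (section 3.5.4), and nothing in the protocol shows arm-dependent recording or attendance. The mismatch with section 3.4 remains. AEs might be called patient-reported and so exempt, but section 3.4 places (S)AE assessment in rater training.

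**Denominators belong in the SAP.** Usually they do. Here section 10.5.9 fixes one, the total number of patients, and carries it over to the period tables. Section 6.3 asks for follow-up after treatment is stopped, which limits loss but does not remove it.

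**Conclusion.** The point holds and is minor. The stated after-treatment incidence treats unobserved patients as event-free. At 10% loss unrelated to AEs, an assumed 30% would be reported as no lower than 27%. An assumed 5% against 15% loss would move the arm difference by up to 3 points, against a 95% interval of about ±15 points. Safety is analysed descriptively.

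The during and after tables should not be read against each other, since length and elicitation both differ and act in opposite directions on counts. Neither a built-in fall in AEs after treatment nor a bias between arms from the contact schedule is supported.

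The conflict between section 3.4 and sections 5.3.1 and 7.2 rests on the text alone. It concerns a blinding property claimed for AE data that the treatment period does not have.

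**What to change.** In section 10.5.9:

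- For the after-treatment tables, use as denominator the safety-set patients still under observation after the end of treatment, including anyone whose event was reported outside a visit. Keep the percentage of the whole safety set alongside, because the restricted denominator conditions on follow-up after randomisation.
- Add AEs per 100 patient-weeks observed, by arm and period.
- State that the during and after tables are not directly comparable because elicitation differs.

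In section 3.4, say that AEs during treatment are collected by unblinded psychotherapists.

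Optionally, record for each AE whether a therapist or a rater reported it, so that rater-recorded AEs can be shown as a supplement. They should not replace the all-source tables, because patients may not repeat to the rater what they have already told the therapist.

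The cost is a few more descriptive tables, two wording changes and one optional eCRF field.

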## 11 Data Safety Monitoring Board (DSMB)

An independent Data Safety Monitoring Board (DSMB) was established before enrolment of the first patient. The members of the DSMB are given in section "Responsibilities". The function of the DSMB is to monitor the course of the trial and if necessary to give a recommendation to the coordinating investigator for continuation, modification or discontinuation of the trial. The underlying principles for the DSMB are ethical and safety aspects for the patients. It is the task of the DSMB to examine, whether the conduct of the trial is still ethically justifiable, whether safety of the patients is ensured, and whether the process of the trial is acceptable. For this the DSMB has to be informed about the patient recruitment, the adherence to the protocol, and the observed adverse events. The composition and responsibilities of the DSMB, the structure, frequency and procedures of its meetings, and its relationship to other key trial team members, will be laid down in a separate DSMB charter.

## 12 Ethical and Legal Principles

### 12.1 Subject Informed Consent

Before enrolment in the study, the subject will be informed that participation is voluntary and that he/she may withdraw at any time without having to give reasons and without penalty or loss of benefits to which the subject is otherwise entitled.

The subject will be given ample time and opportunity to obtain answers to any open questions. All questions should be answered to the satisfaction of the subject. In addition, the subject will be given a "Subject Information Sheet", which contains all the important information in writing.

The subject's written consent must be obtained before any study-specific tests. For this purpose, the written consent form will be personally dated and signed by the study subject and the rater conducting the informed consent discussion.

By signing the consent form, the subject agrees to voluntarily participate in the study and declares that he/she agrees to be contacted for the follow up visits. By signing the form, the subject also declares that he/she agrees to the recording of personal data, particularly medical data, for the study after pseudonymisation.

After signing, the subject will be given one copy of the signed and dated written consent form and any other written information to be provided to the subjects.

## **12.2 Ethical and Regulatory Requirements**

Before the start of the study (enrolment of the first patient), the principal investigator has submitted the study documents to the responsible Ethics Committee in Freiburg for approval. The personnel and facilities' qualifications of the participating sites are verified by the principal investigator before submission to the local ethics authorities (where applicable according to local federal state law). It is not required to obtain authorisation from a competent authority for IPT Work.

## **12.3 Data Protection and Confidentiality**

The pertinent provisions on data protection must be fully complied with.

The study subjects will be informed of the purpose and extent of the collection and use of personal data, particularly medical data.

Findings obtained in the course of the cohort study will be stored on electronic media and treated in strict confidence. For the protection of these data, organisational measures have been taken to prevent disclosure to unauthorised third parties. For example, the subject data will be captured in pseudonymised form (subject ID No. for the particular study, year of birth) throughout the documentation and evaluation phase.

## **12.4 Archiving**

After completion of the trial the Subject identification log and all essential study documents will be retained at the study sites for 10 years. The local PI will be responsible for the archiving compliant to GCP.

After completion of the trial the TMF will be retained at the CI's sites for 10 years. The CI will be responsible for the archiving compliant to GCP

## **13 Registry and Publications**

The Coordinating Investigator has posted the key elements of this protocol in DRKS (DRKS ID: DRKS00035259) before the start of the recruitment phase. Additionally the protocol, will be published after initial approval of the ethics committee in a scientific journal. In addition, upon trial completion the results of this trial will be submitted for publication to a peer-reviewed journal.

Reporting guidelines will be taken into account (see [www.equator-network.org](http://www.equator-network.org)), e.g. the CONSORT statement should be adhered to in the preparation of papers on the results of randomised studies.

Each publication of trial results will be in mutual agreement between the principal investigator, the other investigators involved, the biostatistician and the CTU. All data collected in connection with the clinical trial will be treated in confidence by the coordinating investigator and all others involved in the trial, until publication. Final results may only be published (orally or in writing) with the agreement of the coordinating investigator, the biostatistician and the CTU. This is indispensable for a full exchange of information between the above-named parties, which will ensure that the opinions of all parties involved have been heard before publication. The agreement, which does

not include any veto right or right of censorship for any of the parties involved, may not be refused without good reason.

## 14 Administrative agreements

### 14.1 Financing of the project

The clinical trial is financed by the German Research Foundation (DFG); its project number is 507692077, file reference: SCHR 443/18-1.

This funding source had no role in the design of this study and will not have any role during its execution, analyses, interpretation of the data, or decision to submit results.

### 14.2 Study reports

Starting in December 2024, reports will be periodically submitted to the German Research Foundation (DFG). The interim reports are prepared in accordance with the specifications of the German Research Foundation (Clinical Trials Programme). The interim reports serve to monitor the progress of the approved study on a six months basis and can be submitted to the review group for renewed discussion if the milestones are not reached. Except when required by law, no one will disclose a result of the study to third parties unless all parties involved have first agreed on the results of the analysis and their interpretation.

